#### Inclusion criteria

Aged 11–18Score more than 42 on the UCLA-LS-3 [35], which is more than one standard deviation above the mean in a large community adolescent sample [49].Have a parent/carer who is willing to take part in the study.Report loneliness as their primary difficulty (i.e., they are able to identify relevant goal-based outcomes and their current difficulties are not attributable to a significant mental health problem).

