#### Secondary outcome measures

It will be assessed how many of the participants display a reliable and clinically significant change [38] in total loneliness scores on the UCLA-LS-3 [35] and parent and self-reported impact scores on the SDQ [36]. It will also be examined how many participants display reliable change [38] in parent and self-reported Total Anxiety and Depression Scores on the RCADS [37], as well as how many participants report ‘clinically significant’ and ‘borderline clinical’ scores at baseline and post-intervention.

For the UCLA-LS-3 criterion B will be used to determine clinically significant change [38]. For criterion B, the participant must move within 2 standard deviations of the mean of a non-clinical comparison population. Criterion A and C will not be used due to lack of normative data available for a ‘clinically lonely’ population. The test-retest reliability used for the calculation will be 0.73 [35]. Normative data for the comparison population will be taken from a large-scale adolescent community sample, mean = 32.82, SD = 9.43 [49]. Reliable change will be calculated using Jacobson and Truax [38], whereby the baseline mean is subtracted from the post-intervention mean then divided by the standard error of measurement, giving the Reliable Change Index (RCI). The RCI indicates what would be categorised as clinically reliable improvement or deterioration.

For the RCADS well-defined norms are available [37], with raw scores being converted to age and gender-specific T-scores. A T-score of 65 means the young person is scoring in the top 7% for un-referred young people and is classified as “borderline clinical”. A T-score of 70 means that the young person is in the top 2% of unreferred young people and is described as the “clinical” threshold. The number of participants scoring within the clinical, borderline clinical and non-clinical ranges at baseline and post-intervention will be reported. As this current study has a small sample, the Reliable Change Index (RCI) used will be from a large normative sample [37].

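### The UCLA-LS-3 cut-off for clinically significant change (51.68) is more lenient than the trial's own entry threshold (above 42), so it is uninformative for entrants scoring 43-51 and lets still-eligible scores count as success

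*Protocol article*

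**What the plan says.** Under Inclusion criteria, the protocol article admits young people scoring more than 42 on the UCLA-LS-3, "which is more than one standard deviation above the mean in a large community adolescent sample [49".

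Under Secondary outcome measures, the loneliness outcome is "how many of the participants display a reliable and clinically significant change [38] in total loneliness scores on the UCLA-LS-3". Both parts must be met. For the clinically significant part the article chooses criterion B: "the participant must move within 2 standard deviations of the mean of a non-clinical comparison population". The norms are "mean = 32.82, SD = 9.43", from the same cited community sample as the entry threshold. The reason for choosing B is that "Criterion A and C will not be used due to lack of normative data available for a ‘clinically lonely’ population".

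For the reliable part, the article gives a test-retest reliability of 0.73 and divides the change by the standard error of measurement (SEM). It does not print the value of the criterion B cut-off, and it has no rule for a participant who already satisfies criterion B at baseline.

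**The concern.** Entry and end state are set on one scale from one set of norms, but at different distances from the mean: one SD to get in, two SDs to be classed as non-clinical. The boundary for a good outcome therefore lies on the lonelier side of the boundary for entry.

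Two groups are affected in different ways.

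- **Baseline 43-51.** These participants are eligible and already inside the non-clinical range. If criterion B is an end-state test, it is satisfied before treatment and adds nothing to reliable change. If it requires a crossing, as its wording literally does, they cannot satisfy it however much they improve. The same data then give two different counts.
- **Higher baselines.** A participant can improve reliably, finish at a score that would still admit them to the trial, and be counted as having changed to a clinically significant degree.

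At stake is the count reported for the main loneliness secondary outcome, in a sample where one person makes a visible difference. Aims and objectives names this change as a hypothesis.

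**Working it through.** **Inputs from the protocol article**

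- Entry: UCLA-LS-3 above 42, so whole-number totals of 43 or more (Inclusion criteria)
- Norms: mean 32.82, SD 9.43 (Secondary outcome measures)
- Test-retest reliability r = 0.73 (same section)
- Sample size 6-8 (Participants)

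**Step 1: reproduce the entry threshold.** Mean + 1 SD = 32.82 + 9.43 = 42.25. The lowest eligible score, 43, has z = (43 - 32.82)/9.43 = 1.08. This agrees with the article's description.

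**Step 2: criterion B cut-off.** Mean + 2 SD = 32.82 + 2 x 9.43 = 32.82 + 18.86 = 51.68. This is 51.68 - 42 = 9.68 points above the entry threshold. A score of 51 has z = 1.93 (inside) and 52 has z = 2.03 (outside). All eligible scores from 43 to 51 are inside at baseline; only entrants at 52 or more can cross.

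**Step 3: size of a reliable drop.** Assumptions: the normative SD is used, and the index is compared with 1.96.

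- SEM = SD x sqrt(1 - r) = 9.43 x sqrt(0.27) = 4.90; 1.96 x 4.90 = 9.60 points (denominator as written)
- Standard error of the difference = SEM x sqrt(2) = 6.93; 1.96 x 6.93 = 13.58 points (variant)

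Highest whole-number post score that counts as reliable improvement:

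| Baseline | SEM (drop of at least 9.60) | SE of difference (drop of at least 13.58) |
|---|---|---|
| 43 | 33 | 29 |
| 51 | 41 | 37 |
| 52 | 42 | 38 |
| 53 | 43 | 39 |
| 57 | 47 | 43 |
| 61 | 51 | 47 |
| 65 | 55 | 51 |

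**Step 4: consequences, using the SEM denominator as written.**

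- A change from 51 to 40 (11 points) is reliable. It is a success if criterion B is an end-state test and a failure if a crossing is required.
- A change from 62 to 51 (11 points) is reliable and crosses 51.68, so it is a success, yet 51 would still qualify for entry. Such results first become possible at a baseline of 53 (53 to 43). With the standard error of the difference they begin at 57 (57 to 43).

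**Step 5: how many participants.** The documents give no baseline distribution, so this is a range under assumption. The share is P(42.5 < X < 51.5)/P(X > 42.5) for normal X.

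- Community norms themselves (mean 32.82, SD 9.43): 84%
- Recruited group with mean 48: 66% (SD 6) to 51% (SD 9.43)
- Mean 52: 44% (SD 6) to 38% (SD 9.43)
- Mean 60: 8% (SD 6) to 16% (SD 9.43)

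**Step 6: weight of one person.** 1/8 = 12.5 and 1/6 = 16.7 percentage points.

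**The case against.** The strongest reply is that criterion B never stands alone. A reader might infer from the two thresholds that entrants at 43-51 are already recovered before treatment. The article does not support that: reliable change is also required, so nobody counts as a success at baseline. This part of the reply stands in full.

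A second reply is that the complaint about finishing as high as 51 does not touch entrants at 43-51. A reliable drop from there ends at 41 or lower (37 or lower with the standard error of the difference), which is below the entry threshold. That is also correct. It means the two problems affect different people and should be stated separately. It also means that a cut-off of 42 adds no further discrimination for baselines of 43-51; what it gives them is a single, unambiguous count.

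Third, criterion B is a recognised choice, and the article gives a reason for it. The lack of norms for a lonely clinical population explains why A and C were set aside. It does not explain an outcome line more lenient than the entry line when both come from the same norms.

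Fourth, a reader might conclude that the reported count cannot be interpreted at all. That goes too far. Under the end-state reading, the count is reliable change for baselines of 43-51 and reliable change plus crossing for 52 or more; this is mixed, but readable beside individual scores. The reliable-change component itself is not affected.

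Finally, a reader might extend the point to the SDQ impact scores. The inclusion criteria set no SDQ score, so there is no entry line for that cut-off to contradict, and the documents do not show where entrants would start on it.

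**Conclusion.** The inconsistency is real and follows from the article's own figures. The entry score, criterion, mean and SD are all fixed in the text and conflict with each other, so this is not detail left to an analysis plan. For baselines of 43-51 the clinically significant part of the outcome carries no information or cannot be achieved, depending on the reading. For baselines of about 53 or more (SEM) or 57 or more (standard error of the difference), a reliable improvement can be credited as clinically significant at a score that still meets the entry rule.

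The location of the cut-off needs no assumption. The figures of 53 and 57 rest on the normative SD and a 1.96 multiplier. The share of entrants at 43-51, roughly 8% to 84%, rests entirely on assumed distributions. Its upper end treats entrants as random eligible members of the community sample, which is unlikely when loneliness must be the primary difficulty.

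The point affects one component of one secondary outcome. The primary analysis of the Three-Item Loneliness Scale by visual inspection and Tau-U, and the feasibility criteria, are untouched. It should be corrected, with the weight due to a secondary outcome.

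**What to change.** Amend Secondary outcome measures before any outcome data are seen:

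1. Define clinically significant change on the UCLA-LS-3 as reliable change plus a post-intervention score of 42 or below, which is the trial's own entry line.
2. Report the 2-SD criterion B only for participants with a baseline of 52 or more, and give that number as the denominator.

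A sentence saying how participants already inside 51.68 are counted would settle the first problem alone. It would leave still-eligible post scores counting as success.

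The cost is wording only: no new data, visits or participants. The drawbacks are a stricter target for participants with high baselines and a smaller, possibly very small, denominator for the 2-SD version. Choosing between the readings after seeing 6-8 results would be post hoc, so the timing matters more than the effort.

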### Outcome measures

#### Loneliness

*The three item loneliness scale [34].* This will be used to assess the child/young persons’ self-reported loneliness throughout each of the three phases of the study. The scale is a brief 3-item measure derived from the UCLA-LS-3 [35]. The measure contains three items rated on a 5-point Likert scale (0 = never, 1 = rarely, 2 = sometimes, 3 = often, 4 = very often). Answers are summed to a total score of 0–12, with higher scores indicating a higher level of loneliness. The Office for National Statistics (ONS) have validated a 3-reponse version of this measure with young people ages 10–15 [19]. In qualitative testing of the measure, they identified that the words “companionship” and “isolation” were difficult for some young people to understand. These changes in wording were also used in this study as the age range was similar to that used in the ONS validation. The items used were “How often do you feel that you have no one to talk to?”, “How often do you feel left out?” and “How often do you feel alone?”.

*UCLA Loneliness Scale (UCLA-LS-3) [35].* The measure will be used to assess the child/young person’s subjective experience of loneliness. The instrument consists of 20 items measured on a 4-point scale where the respondents are asked to indicate how frequently the statement is descriptive of them with the options of never, rarely, sometimes, and often. The UCLA-LS-3 has been used extensively in loneliness research, including in intervention studies [25, 55] and has been validated in a large adolescent sample [49]. The psychometric properties include a very high internal consistency (Cronbach’s α’s ranging from .89 to .94) and a good test-retest-reliability (.73 over a 1-year period) [35].

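### The UCLA-LS-3 Reliable Change Index is described with the wrong divisor (standard error of measurement, not of the difference), which contradicts the Jacobson-Truax method it names and, if followed literally, sets the bar too low by a factor of √2

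*Protocol article*

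**What the plan says.** The place is the protocol article, Data analysis, Secondary outcome measures, in the paragraph on the UCLA-LS-3. The method is named: "Reliable change will be calculated using Jacobson and Truax [38"]. The same sentence then explains it: "the baseline mean is subtracted from the post-intervention mean then divided by the standard error of measurement". The paragraph supplies a reliability ("The test-retest reliability used for the calculation will be 0.73") and the only SD given for this scale, that of the community comparison sample ("mean = 32.82, SD = 9.43"). Earlier, under Outcome measures, Loneliness, the article reports that this reliability was measured over one year.

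The paragraph does not mention the standard error of the difference, a √2 factor, or a cut-off for the index. It does not say which SD enters it. No other section restates or corrects the formula. For the RCADS and the SDQ impact score, the same section takes the RCI values from published normative samples, so the formula in words applies only to the UCLA-LS-3.

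**The concern.** A change score is the difference of two measurements, each with its own error. If each score has error SD equal to the SEM, and the errors are independent, the difference has error SD √2 × SEM. The Jacobson-Truax index divides by that quantity. Dividing by the SEM alone inflates every index value by √2, so ordinary retest noise is more readily labelled reliable improvement or deterioration.

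The numerator is also misdescribed. The outcome is a count of participants who change reliably, so the index has to be computed from each person's own two scores, not from phase or group means.

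Reliable and clinically meaningful change on the UCLA-LS-3 is a stated hypothesis under Aims and objectives. With 6 to 8 participants, one misclassified person moves the reported proportion by 1/8 = 12.5 to 1/6 = 16.7 percentage points.

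**Working it through.** The protocol states no threshold in points, so there is no figure of its own to reproduce. The thresholds below follow from its inputs.

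**Inputs from the protocol article**
- r = 0.73 and SD = 9.43 (Secondary outcome measures)
- 6 to 8 participants (Participants)

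**Assumptions**
- The cut-off is |RCI| > 1.96, the two-sided 5% convention. None is stated.
- The normative SD of 9.43 enters the index. It is the only UCLA-LS-3 SD given.
- Errors are normal and independent, and for the error rates the retest correlation over the trial interval is 0.73.

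**Thresholds**
- SEM = SD × √(1 − r) = 9.43 × √0.27 = 4.90
- S_diff = SD × √(2(1 − r)) = 4.90 × √2 = 6.93
- As written: 1.96 × 4.90 = 9.60, so 10 on whole-number scores
- Under the named method: 1.96 × 6.93 = 13.58, so 14 on whole-number scores
- Gap: 13.58 − 9.60 = 3.98 points

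**False reliable change per participant with no true change**
- As written: 2 × [1 − Φ(1.96/√2)] = 2 × [1 − Φ(1.386)] = 16.6%. Improvement only: 8.3%.
- Under the named method: 5.0%. Improvement only: 2.5%.
- Ratio: 16.6/5.0 = 3.3

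**At least one false reliable improver**

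| Participants | As written | Named method |
|---|---|---|
| 6 | 1 − (1 − 0.0829)^6 = 40% | 1 − 0.975^6 = 14% |
| 8 | 1 − (1 − 0.0829)^8 = 50% | 1 − 0.975^8 = 18% |

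**Sensitivity to the assumptions**
- *Cut-off.* At 1.645 the two-sided rates are 24.5% and 10.0%, a ratio of 2.4.
- *SD.* At r = 0.73 and a cut-off of 1.96, the gap is 2.1 points for SD 5 and 5.1 points for SD 12. The ratio of error rates does not change as long as the same SD and r describe both the threshold and the actual noise.
- *Retest interval.* Twelve sessions on the stated schedule take 2 + 4 + 8 = 14 weeks if bi-weekly means twice a week, or 8 + 4 + 8 = 20 weeks if it means every second week. Adding a 12 to 33 day baseline and 12 post-intervention days gives 122 to 143 days, or 164 to 185 days. Either is well short of a year. Suppose the true correlation over that time is higher while the thresholds stay at 9.60 and 13.58:
  - r = 0.80: the SD of the difference is 9.43 × √0.40 = 5.96. The rates are 2 × [1 − Φ(9.60/5.96)] = 10.7% and 2 × [1 − Φ(13.58/5.96)] = 2.3%.
  - r = 0.865: the SD of the difference is 9.43 × √0.27 = 4.90. The rates are 5.0% and 2 × [1 − Φ(13.58/4.90)] = 0.6%.

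**The case against.** **The clause may be only a mislabelled gloss.** The operative instruction is the named method, and the explanation is loose in its use of means as well. The analyst may well apply the right divisor. A reader might infer that the trial will certainly classify participants at 9.6 points. The text does not establish that. It establishes that the description contradicts the named method, with this effect if it is followed. Since both inputs are supplied beside it, following it is easy, and the contradiction needs removing either way.

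**The error rates are not established for this trial.** This stands in part. A reader might take a tripling of false positives, or a 50% chance of a false improver among 8, as fact. Those figures need the 1.96 cut-off and a retest correlation of 0.73, and the latter is a one-year value. At a correlation of 0.865 the 9.6-point bar would give about 5% by coincidence. The factor of √2 depends on none of this.

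**The outcome is a joint one.** The count combines reliable change with criterion B, under which "the participant must move within 2 standard deviations of the mean of a non-clinical comparison population", that is 32.82 + 2 × 9.43 = 51.68 or below. The rates above concern the reliable-change part only. If criterion B requires crossing 51.68, it removes some false positives. If ending below it is enough, anyone who enters at 43 to 51 already satisfies it at baseline, and reliable change is the only working test for them. The protocol's wording does not settle which is meant.

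**Wider readings fail.** One might infer that the RCADS and SDQ indices share the error. They use published values. One might also add regression to the mean from entry scores above 42. That is a separate design question, and quantifying it would treat volunteers who report loneliness as their primary difficulty as random draws from a community sample, which the documents do not support.

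**Conclusion.** The formula is wrong as written and contradicts the method named in the same sentence. What holds without further assumption is that a literal reading lowers the bar for reliable change by a factor of √2 and puts means where individual scores belong.

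With SD 9.43, r = 0.73 and an assumed cut-off of 1.96, the bar is 10 whole points instead of 14. If 0.73 also holds over the trial interval, false reliable change is about 3.3 times the nominal rate (2.4 times at a 1.645 cut-off). Absolute rates are lower if scores are more stable over the trial's months than over a year.

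The scope is one secondary outcome. The Tau-U primary analysis, the RCADS and SDQ indices and the feasibility criteria are untouched.

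**What to change.** Replace the sentence describing the calculation with: RCI = (individual post-intervention score − individual baseline score) / [SD × √(2 × (1 − r))], and drop the references to means. State the three values beside it: SD 9.43, r 0.73, and the cut-off. At 1.96, a participant must change by at least 14 whole points, a fall counting as improvement. Make the change before any participant is classified.

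The cost is one sentence and a less favourable responder threshold. No extra data are needed, and the published RCI values for the RCADS and SDQ stay as planned.

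### The UCLA-LS-3 reliable-change rule divides by the standard error of measurement instead of the standard error of a difference, so the bar as written is 29% too low

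*Protocol article*

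**What the plan says.** Under Secondary outcome measures, the protocol article sets the UCLA-LS-3 endpoint as a count of individuals: "It will be assessed how many of the participants display a reliable and clinically significant change". The clinical-significance half uses criterion B, under which "the participant must move within 2 standard deviations of the mean of a non-clinical comparison population". The comparison norms are a mean of 32.82 and an SD of 9.43. On reliability, the section says: "The test-retest reliability used for the calculation will be 0.73".

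The reliable-change half is attributed to the Jacobson and Truax method and then spelled out: "the baseline mean is subtracted from the post-intervention mean then divided by the standard error of measurement". The section gives no cut-off for the index and no threshold in scale points. Nothing elsewhere in the article mentions the standard error of a difference.

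**The concern.** There are two defects in one sentence.

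- **Denominator.** The standard error of measurement (SEM) describes the error in one reading. The change from baseline to post-intervention is the difference of two readings, each with its own error. Dividing by the SEM treats one of them as error-free and makes the index too large.
- **Numerator.** The sentence subtracts means, but the endpoint counts participants, and each participant needs an index built from their own two scores.

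Reliable and clinically meaningful change on the UCLA-LS-3 is a stated hypothesis (Aims and objectives), and it is the article's only per-person reliable-change rule for loneliness. With 6–8 participants, one or two people wrongly classed as improved would visibly change the reported result.

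**Working it through.** The plan prints no point threshold for the UCLA-LS-3, so there is no figure of its own to reproduce.

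**Inputs from the article**
- SD 9.43, mean 32.82 and r = 0.73 (Secondary outcome measures)
- Entry score above 42 (Inclusion criteria)
- 6–8 participants (Participants)

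**Assumptions, not stated in the article**
- The cut-off is |RCI| > 1.96.
- The normative SD of 9.43 is the SD that goes into the SEM.

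**Standard errors**
- SEM = SD × sqrt(1 − r) = 9.43 × sqrt(0.27) = 4.90
- S_diff = sqrt(2) × SEM = 6.93
- SEM / S_diff = 1/sqrt(2) = 0.707, so the bar as written is 29.3% too low. SD, r and the cut-off all cancel from this ratio.

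**Bar in points at 1.96**
- As written: 1.96 × 4.90 = 9.60, i.e. 10 or more whole points
- With S_diff: 1.96 × 6.93 = 13.58, i.e. 14 or more whole points

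**False reliable improvement in a participant with no true change, before selection at entry**
- As written: P(Z > 1.96/sqrt(2)) = 8.3% (two-sided 16.6%)
- With S_diff: P(Z > 1.96) = 2.5% (two-sided 5.0%)
- Ratio: 3.3. It depends on the assumed cut-off: 2.4 at 1.645 and 1.8 at 1.28.

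**The combined endpoint.** Criterion B puts the limit at 32.82 + 2 × 9.43 = 51.68. A simulation used normal true scores and errors with the protocol's mean, SD and r, entry above 42, and no true change. Scores were either rounded to whole points or left continuous.

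| No true change, entry above 42 | As written | With S_diff | Ratio |
|---|---|---|---|
| Reliable improvement (rounded scores) | 19.8% | 7.2% | 2.7 |
| Reliable improvement and crossing 51.68 (rounded scores) | 4.5% | 1.9% | 2.3 |
| Reliable improvement and crossing 51.68 (continuous scores) | 3.9% | 1.7% | 2.3 |

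With the rounded rates, the chance of at least one false responder on the combined endpoint is:
- n = 6: 1 − (1 − 0.0447)^6 = 24%, against 1 − (1 − 0.0192)^6 = 11%
- n = 8: 31%, against 14%, by the same formula

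**The case against.** **The method is named, and the sentence is only a gloss.** An analyst who follows Jacobson and Truax rather than the description would compute the index correctly, so this may be a wording error. That is fair as to intent. But the article names a method and then spells out a different calculation. Two analysts could report different counts and both claim to have followed the plan.

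**A reader might infer that the plan compares group means and so cannot yield a count.** The article says mean, not group mean, and the same section fixes the unit as the participant, both in the count and in criterion B. This is a conflict of wording to correct. It plays no part in the 29%, which comes from the denominator alone.

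**A reader might infer that false responders triple.** The 3.3-fold figure applies only to the reliable-change component, at an assumed cut-off and before selection. A UCLA-LS-3 responder must also meet criterion B. People who enter at 43–51 are already inside the 51.68 limit and cannot cross it, which is why the combined figure is nearer 2.3-fold.

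**A reader might infer that drops of 10 to 13 points are known to be noise.** The documents do not establish that. The 0.73 is a one-year retest coefficient (Outcome measures, Loneliness) and may include real change. The same paragraph gives alphas of .89 to .94. With SD 9.43 and the correct formula, these would put the 1.96 bar at about 8.7 and 6.4 points. The 29% shortfall holds for any r, but the absolute error rates assume that 0.73 reflects measurement error alone.

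**The correction does not bring the error rate to 2.5%.** This also stands. Participants are selected for high scores on the same scale, and regression to the mean leaves 7.2% in the simulation even with S_diff.

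**Conclusion.** The description of the UCLA-LS-3 index is wrong as written and nothing else in the article corrects it. The 29% shortfall in the bar is exact and needs no assumption. The other sizes are conditional:

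- The 9.60 against 13.58 points assumes SD 9.43, r 0.73 and a cut-off of 1.96.
- The 8.3% against 2.5% also assumes normal errors, no true change and no selection at entry.
- The roughly 2.3-fold inflation for the combined endpoint rests on the simple normal model with entry above 42 and reads criterion B as a crossing of 51.68.

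The reach is limited to one secondary outcome. The primary outcome, the Three-Item Loneliness Scale analysed by visual inspection and Tau-U, is untouched. The RCADS and SDQ indices are taken from published norms, so this sentence does not govern them.

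**What to change.** Replace the sentence with: *For each participant, RCI = (post-intervention score − baseline score) / (SD × sqrt(2) × sqrt(1 − r)), with SD = 9.43 and r = 0.73; reliable change is |RCI| > 1.96.* State the resulting threshold, which is a change of 14 or more points under these inputs.

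This supplies the missing cut-off, fixes which SD is used, and removes the conflict between means and a per-participant count. It costs one sentence and needs no new data. The price is that the responder count on this secondary outcome may be less favourable.

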For the SDQ parent and self-reported impact scores criterion C will be used to calculate clinically significant change. For criterion C, the participant’s score must move to the comparison side of the point halfway between the clinical and comparison group mean. Criterion C will be calculated as both clinical and comparisons norms are available. A test-retest reliability of .71 will be used [69]. For parent-report M = 0.4, SD = 1.1 will be used for comparison norms [36] and M = 6.2, SD = 2.7 for clinical norms [70]. For child report M = 0.2, SD = 2.8 will be used for comparison norms [36] and M = 5, SD = 3.3 [70] for clinical norms. For the SDQ impact scores, the Reliable Change Index (RCI) values will be based on those reported by Goodman [36] from a large normative sample.

The VAS and GBO’s will also be visually presented and the means and standard deviations of scores at baseline and post-intervention will be reported.

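### The child comparison SD for the SDQ impact score (2.8 with a mean of 0.2) is not feasible, and the midpoint wording of criterion C ignores the unequal SDs listed beside it, which moves the parent cut-off from 2.08 to 3.30

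*Protocol article*

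**What the plan says.** The Data analysis section, under Secondary outcome measures, counts participants with reliable and clinically significant change on the parent- and self-reported SDQ impact scores, citing the Jacobson–Truax method. Criterion C is chosen for the SDQ, and the score "must move to the comparison side of the point halfway between the clinical and comparison group mean".

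The norms are:

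- Parent: "For parent-report M = 0.4, SD = 1.1 will be used for comparison norms [36"] and "M = 6.2, SD = 2.7 for clinical norms [70"].
- Child: "For child report M = 0.2, SD = 2.8 will be used for comparison norms [36"] and "M = 5, SD = 3.3 [70] for clinical norms".

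On reliable change the same paragraph says "A test-retest reliability of .71 will be used [69"], and then that "the Reliable Change Index (RCI) values will be based on those reported by" a cited normative study, which is also the source of the comparison norms. No cut-off value is printed. The description of the SDQ under Psychological wellbeing gives no score range for the impact scale.

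**The concern.** Two things in this paragraph look wrong.

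- **The child comparison norm.** The SD is fourteen times the mean (2.8/0.2) on a score that cannot be negative. The parent norm from the same source has a larger mean (0.4) and a much smaller SD (1.1).
- **The criterion C rule.** A midpoint uses no SD, yet an SD is given for every norm. With unequal SDs, the cut-off in the cited method is the point that lies equally many SDs from each mean, and that is not the midpoint.

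A third matter is less clear. The paragraph gives both a reliability and a published source for the reliable change index (RCI), without saying how the two fit together.

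Aims and objectives makes reliable and clinically meaningful change in SDQ impact a stated hypothesis, reported as a count among 6–8 participants. One participant classed differently moves the proportion by 12.5 points (1/8) to 16.7 points (1/6).

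**Working it through.** **Inputs** (all from Secondary outcome measures). Parent: comparison M0 = 0.4, S0 = 1.1; clinical M1 = 6.2, S1 = 2.7. Child: comparison M0 = 0.2, S0 = 2.8; clinical M1 = 5, S1 = 3.3. Reliability r = .71. Assumptions: scores start at 0 and are whole numbers. The scale maximum K is not stated, so a range is shown.

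**1. Is the child SD feasible?** For a score between 0 and K, x² ≤ Kx, so the variance is at most m(K − m) and the SD at most √(m(K − m)). With m = 0.2:

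| Scale maximum K | Largest possible SD |
|---|---|
| 6 | 1.08 |
| 10 | 1.40 |
| 20 | 1.99 |
| 30 | 2.44 |
| 39 | 2.79 |

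An SD of 2.8 needs K ≥ 0.2 + 2.8²/0.2 = 39.4. The parent pair needs only K ≥ 0.4 + 1.1²/0.4 = 3.4, so it raises no problem. Clinical means of 5 and 6.2, on a scale covering a few domains of daily life, make a maximum near 40 implausible.

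**2. The protocol's own rule, the midpoint (M0 + M1)/2.**

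- Parent: (0.4 + 6.2)/2 = 3.30, pass mark ≤3.
- Child: (0.2 + 5)/2 = 2.60, pass mark ≤2.

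**3. The SD-weighted criterion C.** Setting (C − M0)/S0 = (M1 − C)/S1 gives C = (S0·M1 + S1·M0)/(S0 + S1), which equals the midpoint when S0 = S1.

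- Parent (SD ratio 2.7/1.1 = 2.45): (1.1 × 6.2 + 2.7 × 0.4)/3.8 = 7.90/3.8 = 2.08, pass mark ≤2.
- Child, printed SDs (ratio 3.3/2.8 = 1.18): (2.8 × 5 + 3.3 × 0.2)/6.1 = 14.66/6.1 = 2.40, pass mark ≤2.
- Child, largest SD feasible on 0–10: (1.4 × 5 + 3.3 × 0.2)/4.7 = 7.66/4.7 = 1.63, pass mark ≤1. Smaller SDs lower it further. At 0.4 the cut-off is 2.66/3.7 = 0.72, pass mark 0.

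A parent score of 3 lies (3 − 0.4)/1.1 = 2.4 SDs above the comparison mean and (6.2 − 3)/2.7 = 1.2 SDs below the clinical mean. It is on the comparison side of the midpoint but nearer, in SD units, to the clinical group.

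**4. What an SD-based RCI would give.** The protocol prints no RCI formula for the SDQ. With the standard error of the difference, the threshold is 1.96 × SD × √2 × √(1 − .71).

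- Child, SD 2.8: 4.18 points, so a change of at least 5 whole points.
- Child, SD 1.4: 2.09 points, so at least 3. A smaller SD gives a lower threshold.

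**The case against.** The best defence is that, read literally, the faulty SD does nothing. A midpoint contains no SD, so the child cut-off is 2.60 whatever the comparison SD is, and the RCI is said to rest on published values. This stands. A reader might infer that the child classification is already wrong because of the 2.8. The text does not support that, because the SD matters only through a weighted cut-off or an SD-based RCI.

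Three further stronger readings also go too far:

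- **That the SDs differ by a factor of about 2.5 on both versions.** That ratio belongs to parent report. The printed child ratio is 1.18, and the two rules then give the same whole-score pass mark.
- **That a parent score of 3 would by itself count as recovery.** The protocol requires reliable change as well, so the choice of rule affects only a participant who ends at 3 and also meets the RCI.
- **That the two statements on the RCI contradict each other.** They may mean norms from one source combined with a reliability from another. The cited sources are not available here, so this is an ambiguity to clear up.

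It can also be said that the midpoint wording is a loose gloss in a condensed article and that the weighted formula is intended. That is possible, since the listed SDs otherwise have no use in the cut-off. But then the infeasible child SD enters the calculation directly, so this defence removes one problem by making the other matter.

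**Conclusion.** The point holds in limited form. The child comparison norm is infeasible as printed for any non-negative scale with a maximum below 39.4. This does not depend on the assumed 0–10 range, which serves only to give the ceiling of 1.40. The correct value cannot be settled from the protocol, so no corrected child cut-off can be given here.

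The midpoint is a choice of formula that departs from the method invoked when SDs are unequal. It makes the parent cut-off 3.30 − 2.08 = 1.22 points more lenient, or one whole score. For child report, the printed SDs make no difference to the pass mark.

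This should be fixed before analysis, but it does not endanger the trial's main conclusions. The SDQ impact counts are descriptive and secondary, and neither the Tau-U analysis of the primary outcome nor the feasibility criteria depend on them.

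**What to change.** 1. Check the child comparison SD against its source and correct it.
2. Replace the midpoint wording with C = (S0·M1 + S1·M0)/(S0 + S1) for both informants. The parent cut-off is then 2.08; the child cut-off is to be recomputed with the corrected SD.
3. State whether the RCI uses the published values or r = .71 with the corrected comparison SD, and give the formula.
4. Print the resulting whole-score thresholds for parent and child report before outcome data are seen, so that no choice between cut-offs is made afterwards.

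The cost is one look-up and a few lines of text. The downside is a slightly stricter threshold for clinically significant change: on parent report a final score of 2 or less instead of 3 or less.
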